### Cohorts

 Participants will be recruited into three separate cohorts. The recruitment target detailed for each cohort allows for a 20% attrition rate over the course of the study. These cohorts will be:

Healthy control participants, defined as participants with MMSE scores of >26 and with the absence of any regular memory complaints/symptoms or any signs or symptoms suggestive of dementia.Participants with early DLB include:Those who meet research criteria for the diagnosis of MCI-LB.^14^Those who meet criteria for mild DLB (CDR score of 0.5 or 1).^5^Participants with early AD include:Those who meet diagnostic criteria for MCI-AD.^13^Those who meet diagnostic criteria for mild AD dementia (CDR score 0.5 or 1).^6^

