### Clinical assessment, neuropsychological battery and informant questionnaires

 At all three study visits, detailed neuropsychological testing and informant questionnaires are undertaken using the battery outlined in table 1. The neuropsychological assessment battery is consistent between cohort groups in order to allow for between-group comparisons. The collection of clinical and demographical information is taken at the same time as the neuropsychological testing.

**Table 1 T1:** Neuropsychological testing

Assessment type	Assessment name	Format	Purpose
Neuropsychological assessments	Addenbrooke’s cognitive examination revised^89^	Researcher-administered structured test	Multidomain cognitive screening tool
	Montreal Cognitive Assessment^90^	Researcher-administered structured test	Multidomain cognitive screening tool
	Trails A and B^91^	Researcher-administered structured test	Assessment of executive function
	Rey auditory verbal learning test^92 93^	Researcher-administered structured test	Assessment of verbal episodic memory
	Feeling of presence questionnaire^94^	Researcher-administered questionnaire	Assessment of presence hallucinations
	Noise Pareidolia Test^95^	Researcher-administered structured test	Assessment of visual hallucination-like illusions
Motor assessment	MDS-UPDRS part III (motor subscale)^96^	Performed by study clinician or trained researcher	Measure of Parkinsonism (motor aspects)
Psychiatric symptom questionnaires	Hospital Anxiety and Depression Scale^97^	A 14 item self-reported questionnaire	Assessment of symptoms of anxiety and depression
	Geriatric Depression Scale^98^	A 30 item self-reported questionnaire	Assessment of depressive symptoms
Informant questionnaires	Cambridge Behavioural Inventory, revised^99^	An 81-item carer-reported questionnaire	Assessment of several behavioural abnormalities in the everyday life including impulsivity and apathy
	Bristol Activities of Daily Living Score^100^	A 20-item carer-reported questionnaire	Measure of ability of person with dementia to carry out activities of daily living
	Neuropsychiatric Inventory^101^	Researcher administered, carer-reported 13 item screening tool	Assessment of psychopathology in people with brain disorders
	Clinician Assessment of Fluctuation^102^	Researcher administered, carer-reported with two screening questions and two rating questions	Assessment of conscious level and degree of symptomatic arousal fluctuation

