### Analysis

 The authors have an extensive background of completing and analysing data from longitudinal research studies in these and similar populations. For example, the NIMROD study^82^ consisted of deep phenotyping and neuroimaging with longitudinal cognitive assessments, exploring the role of brain inflammation in dementia.^83 84^ The aim of this study is to detect differences in immune profiles between cohorts. The continuous variable of cognitive decline, as measured by the battery of neuropsychological assessments, as well as the binary progression to dementia from MCI, is also the outcome of interest. Multivariate statistical techniques alongside high-dimensional clustering, annotation and differential analysis^85^ will be employed to analyse immune cell counts and clinical measures in order to identify key combinations of immune cell clusters that are predictive of disease phenotype and rate of decline.^86^ This procedure will also reduce the dimensionality of the data. Alongside this, standard automated and/or manual gating, followed by parametric/non-parametric tests, will be applied, depending on the distribution of the data sets. Markers of inflammation, τ, phosphorylated-tau, Aβ and α-synuclein from bio-samples, will be compared using standard parametric methods. Cognitive and biomarker data will also be compared between healthy control, MCI-DLB/mild DLB and MCI-AD/mild AD groups in order to identify any group-level differences. Neuropsychological test scores will be converted to domain z scores for correlational analysis with biomarker and clinical data. Repeat measures from follow-up assessments will be normalised to control scores at baseline and change scores correlated with baseline changes to determine predictors of decline. If multiple predictors of decline are identified, regression and other multi-variate statistical methods including mixed effects models will be used to determine the key predictors. Genetic analysis will be used for confirmatory genetics of alleles known to be associated with inflammation or neurodegeneration and for exploratory analyses within collaborative studies.

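### Predictors of cognitive decline are found by correlating change scores, and mixed models follow only if several are found, so the less precise step decides what reaches the model that uses all three visits

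*Protocol article*

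**What the plan says.** The protocol article, Analysis section, gives an order of work for decline. First, in order to find its predictors: "Repeat measures from follow-up assessments will be normalised to control scores at baseline and change scores correlated with baseline changes". Then: "If multiple predictors of decline are identified, regression and other multi-variate statistical methods including mixed effects models will be used to determine the key predictors". The outcome is described as "The continuous variable of cognitive decline, as measured by the battery of neuropsychological assessments", alongside progression from MCI to dementia.

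The same section has a second route that carries no condition. Multivariate and clustering methods are to "identify key combinations of immune cell clusters that are predictive of disease phenotype and rate of decline". No longitudinal model is named for it.

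On the data available, the section on clinical assessment says: "At all three study visits, detailed neuropsychological testing and informant questionnaires are undertaken using the battery outlined in table 1". The Overview of protocol puts the repeat visits at 18 months and 3 years, and the Summary says that 3-year outcomes will be obtained where possible. The Cohorts section says that the recruitment target "allows for a 20% attrition rate over the course of the study". All cohorts, controls included, take the same battery.

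**The concern.** A change score is the difference between two visits, and this study has three. An 18-month change leaves out the 3-year data. A 3-year change leaves out the 18-month data and everyone lost after that visit. The article does not say which is meant, but either choice discards information. A mixed model would keep it, including the 18-month score of someone not seen at 3 years.

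The order makes this matter. The mixed model is reached only if the correlations have already found several predictors. A marker that the weaker step misses is not carried forward, and if just one predictor is found the text triggers no mixed model at all.

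The predictor is also unclear: *baseline changes* is not a defined quantity, since a value measured once at baseline is not a change. What is at stake is the part of research question 2 that links immune markers to disease progression.

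**Working it through.** **1. The plan's own correlation figures.** Fisher z, two-sided 5%, 80% power: n = ((1.960 + 0.842)/atanh r)² + 3.
- r = 0.5: (2.802/0.5493)² + 3 = 29.0. The stated 29 reproduces.
- r = 0.35: (2.802/0.3654)² + 3 = 61.8. At n = 60 the detectable r is 0.355 and power is 79 to 80%. The stated 60 reproduces within rounding.
- If 60 is the number recruited and 20% have no change score, 48 remain. Power at r = 0.35 is then about 70% and the detectable r is 0.395. If 60 already means completers (60/0.8 = 75 recruited), there is no shortfall. The article does not show which applies.

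**2. How much of a true slope a change score captures.** The documents give no variance components, so these are assumed, on a z-score scale: slope SD s per year, residual SD e, visits D years apart. The reliability of the annualised change is s²/(s² + 2e²/D²). The observed correlation is the marker–slope correlation times the square root of that. With marker–slope correlation 0.5:

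| s, e | Reliability, 18 months | Observed r | Reliability, 3 years | Observed r |
|---|---|---|---|---|
| 0.3, 0.4 | 0.09/(0.09 + 0.142) = 0.39 | 0.31 | 0.09/(0.09 + 0.036) = 0.72 | 0.42 |
| 0.3, 0.6 | 0.09/(0.09 + 0.320) = 0.22 | 0.23 | 0.09/(0.09 + 0.080) = 0.53 | 0.36 |
| 0.2, 0.4 | 0.04/(0.04 + 0.142) = 0.22 | 0.23 | 0.04/(0.04 + 0.036) = 0.53 | 0.36 |

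**3. Simulated power for those rows.** 60 per group, 10% lost before 18 months and about 20% by 3 years, 400 runs per scenario (Monte Carlo error about 2 points). The mixed model has a random intercept and slope and tests marker × time. It was fitted with the true variances, which favours it slightly. Each cell gives dropout at random, then dropout after 18 months depending on observed decline.

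| s, e | 18-month change | 3-year change | Mixed model, all visits |
|---|---|---|---|
| 0.3, 0.4 | 62%, 66% | 86%, 82% | 89%, 90% |
| 0.3, 0.6 | 36%, 43% | 74%, 73% | 75%, 76% |
| 0.2, 0.4 | 42%, 37% | 73%, 73% | 77%, 79% |

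Fisher z gives much the same for the change scores. For the first row, r = 0.31 with 54 people gives 63%, and r = 0.42 with 48 gives 86%. From the unrounded results, the mixed model gains 24 to 42 points over the 18-month change and 1 to 8 over the 3-year change. The low end of the second range is within Monte Carlo error.

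**4. Other assumptions.**
- Marker–slope correlation 0.35, s = 0.35, e = 0.45, dropout depending on earlier scores, about 47 of 60 completing, mixed model fitted by REML, 300 runs: 36% (18-month change), 50% (3-year change), 63% (mixed model). The gains are 27 and 13 points.
- A further run with 60 per group and assumed variances gave gains of about 15 to 32 and 2 to 9 points.

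**5. Bias.** In the 300-run scenario the completers' slope was 0.113 against a true 0.1225, an attenuation of 1 − 0.113/0.1225 = 8%; the mixed model gave 0.126. In the step 3 scenarios with decline-dependent dropout, the 3-year change gave 0.145 and 0.149 against 0.150, and 0.097 against 0.100, so 1 to 3%. The further run gave about 5 to 8% with strong dependence of dropout on decline and about 0 to 2% without it.

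**6. Retest gain.** If everyone in a group gains the same amount g on retesting, each change becomes change + g. Adding a constant leaves the within-group correlation with a marker unchanged.

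**The case against.** The strongest reply is that a condensed article need not say which visit enters the change score, how missing follow-up is handled, or which covariates are used. That stands, and none of those omissions is counted here. The article does fix the order of the two steps, and that is the point. It is also fair that mixed models are already named, and that the multivariate route to rate of decline has no condition. So the correlations are not the only way a marker could surface, though that route names no longitudinal model either.

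A second reply concerns the power figures. They set the correlation with the true slope, so the observed correlations fall below the 0.35 to 0.5 that the Power calculation section has in mind. With 47 completers, Fisher z gives about 68% power at an observed r of 0.35, 73% at 0.37 and 95% at 0.5. This stands: the simulated powers are not forecasts for this study. The comparison between methods on the same simulated data is what carries the point.

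Four stronger readings are tempting and are not supported:
- *The results will be biased because fast decliners drop out.* The documents give an attrition rate and nothing on who leaves. Step 5 shows appreciable attenuation only under strong dependence on earlier decline. A mixed model also recovers little about slope from people seen only at baseline.
- *Practice effects corrupt the search for predictors.* By step 6, a gain shared within a group cancels. It matters for the size of decline, for pooled or between-group comparisons, or where the gain varies with severity. Scaling by controls' baseline does not prevent their own change from being computed.
- *The first step is an unadjusted p-value screen.* The text says only that predictors are identified.
- *Research question 2 as a whole is undermined.* It also asks how immune markers change over time, which this point does not touch.

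**Conclusion.** The concern holds as a matter of method and order. A less precise step decides whether a more suitable model, already named in the plan, is used at all, in a study with three cognitive visits and expected attrition.

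The harm is mainly lost precision, and its size depends on a choice the article leaves open. It is large if the 18-month change is used (roughly 15 to 40 power points). It is small if the 3-year change is used (about 1 to 9 points, 13 in the least favourable scenario). All these figures rest on assumed variances and dropout with 60 per group. Bias is conditional on how people drop out and is not shown by the documents. The undefined predictor, *baseline changes*, is a separate wording fault that should be corrected at the same time.

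**What to change.** - Make a linear mixed model on all available visits the main analysis of predictors of decline, for each candidate marker. Use a random intercept and slope and a baseline marker × time term, adjusted for age and sex as in the planned analysis of covariance.
- Remove the condition that several predictors must first be identified.
- Keep the change-score correlations as descriptive, and state which visit they use.
- Replace *baseline changes* with *baseline marker values*.
- Treat z-scaling by controls' baseline as a unit only. Where the size of decline or group differences in decline are reported, include controls with a cohort × time term, so that patients' change is set against controls' change at the same visits.

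The cost is a change of analysis wording and modest extra modelling. No new data are needed, and the article says that full analyses await the end of the study, so the order can still be changed.

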### Power calculation

Our aim is for the study to have 80% power to detect differences in proportions of immune cell populations between groups at an alpha of 0.05. For an analysis of covariance with three groups and two covariates (age and sex), a sample size of 90 (30 in each group) would give sufficient power to detect an effect size of 0.33 (Cohen’s f, equivalent to Cohen’s d ~0.35). A sample size of 180 (60 in each group) would detect an effect size of 0.23 (Cohen’s f, equivalent to Cohen’s d ~0.24). By using data from previously published work performed by this group, which investigated myeloid cell subsets using flow cytometry in the NIMROD cohort,^87^ we estimated the effect sizes for significant immune cell differences between DLB, AD and controls to be between Cohen’s D 0.5–0.8. This suggests that sample sizes above 30 per group would be sufficient to detect these differences, with larger sample sizes detecting more subtle differences.

For correlations with cognition, Gate *et al*^75^ identified with mass cytometry immune cell populations in AD correlating with cognitive scores with slopes of magnitude ~0.5. A similar magnitude of correlations (r = 0.37–0.64) has been shown with immune cell subsets detected by mass cytometry and cognitive decline in AD.^88^ To detect correlations of this magnitude would require a sample size of 29 in each group (80% power at alpha = 0.05). A sample size of 60 in each group would detect the more modest correlations ~0.35 (all power calculations performed in G*Power v3.9.7.1).

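### The stated Cohen's d equivalents are about half what the Cohen's f values imply, so 30 per group is not enough for the lower part of the planning range d = 0.5–0.8

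*Protocol article*

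**What the plan says.** The Power calculation section of the protocol article sets its target as follows: "Our aim is for the study to have 80% power to detect differences in proportions of immune cell populations between groups", with alpha 0.05. The model is "an analysis of covariance with three groups and two covariates (age and sex").

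Two sample sizes are considered:

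- For the first, 90 in total or 30 per group, the detectable effect is given as "an effect size of 0.33 (Cohen’s f, equivalent to Cohen’s d ~0.35").
- The second, 180 in total or 60 per group, is said to detect "an effect size of 0.23 (Cohen’s f, equivalent to Cohen’s d ~0.24").

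The section then turns to the group's earlier flow cytometry data: "we estimated the effect sizes for significant immune cell differences between DLB, AD and controls to be between Cohen’s D 0.5–0.8". From the two together it concludes: "This suggests that sample sizes above 30 per group would be sufficient to detect these differences". Larger samples are presented as serving only subtler effects.

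**The concern.** Cohen's f and Cohen's d are on different scales. For two equal groups d is exactly 2f, and for three groups the ratio of the largest mean difference to f is larger still. A d almost equal to f cannot be right.

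The slip matters because the conclusion is a comparison on the d scale. If 30 per group really detected d of about 0.35, the whole range 0.5–0.8 would be comfortably covered. If the detectable d is about twice that, most of the range lies below it. This comparison is the section's sample-size argument for the main aim, which is to find immune differences between the cohorts. A reader who accepts it could take a null result at 30 per group as evidence against an effect of d = 0.5 that the study had about an even chance of missing.

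**Working it through.** **Inputs** (all from the Power calculation section): three equal groups, two covariates, alpha 0.05, target power 80%, N = 90 or 180, stated f = 0.33 and 0.23, stated d of about 0.35 and 0.24, anticipated d = 0.5–0.8. Sidedness is not given; pairwise tests are taken as two-sided.

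**Step 1: reproduce the plan's f values.** Noncentral F with numerator df 2, denominator df N − 5 and noncentrality λ = N·f².

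- N = 90, f = 0.33: λ = 90 × 0.1089 = 9.80, power 79.2%. The f giving exactly 80% is 0.333.
- N = 180, f = 0.23: λ = 180 × 0.0529 = 9.52, power 78.8%. The f giving exactly 80% is 0.233.

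The f values are therefore correct to rounding.

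**Step 2: convert f to d.** Let d be the difference between the largest and smallest group means in SD units. The extremes for three equal groups are:

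- means evenly spaced: f = d/√6, so d = f·√6;
- two means equal, one apart: f = d·√8/6, so d = 6f/√8.

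| f | two equal, one apart | evenly spaced | two-group rule d = 2f | stated d |
|---|---|---|---|---|
| 0.33 | 0.70 | 0.81 | 0.66 | ~0.35 |
| 0.23 | 0.49 | 0.56 | 0.46 | ~0.24 |

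The correct d is 2.0 to 2.3 times the stated one (1.9 times by d = 2f). The stated values agree with f/√(1 − f²), which gives 0.350 and 0.236 from the printed f values, or 0.353 and 0.240 from the unrounded 0.333 and 0.2334. That expression has the form of the correlation-to-d formula 2r/√(1 − r²) without its factor 2. How the slip arose is conjecture, and the point does not depend on it.

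**Step 3: power on the d scale.** The omnibus test is as in step 1, with f taken from d under the two mean patterns. For d = 0.5, f is 0.204 or 0.236, so λ is 3.75 or 5.0 at N = 90. The pairwise test is a two-sample t test with noncentrality d·√(n/2) and 2n − 2 df. For d = 0.5 and n = 30 the noncentrality is 0.5 × √15 = 1.94.

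| Per group | d | Omnibus power | Pairwise power |
|---|---|---|---|
| 30 | 0.35 | 20–26% | 27% |
| 30 | 0.5 | 38–49% | 48% |
| 30 | 0.8 | 78–89% | 86% |
| 60 | 0.24 | 20–25% | 26% |
| 60 | 0.5 | 68–81% | 78% |

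The pairwise d detectable with 80% power is 0.74 at 30 per group and 0.52 at 60. For 80% power at d = 0.5 the study needs 64 per group pairwise, or 59–79 for the omnibus test.

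**Step 4: try lenient readings at d = 0.5, 30 per group.**

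- Taking f = d/2 = 0.25 gives 54% power.
- A one-sided pairwise test gives 61%.
- If 0.5 is unadjusted and the covariates shrink the residual SD, age and sex would have to explain 1 − (0.5/0.70)² = 49% (two means equal) to 1 − (0.5/0.81)² = 62% (evenly spaced) of the outcome variance to reach the target. To make the stated d = 0.35 itself right they would have to explain 1 − (0.35/0.70)² = 75%. The plan assumes no such figure.

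None of these reaches 80% on the plan's own assumptions.

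**The case against.** The strongest counter-argument is that the range 0.5–0.8 comes from a source not shown, and the section does not say how it was computed. If it came from the same faulty conversion, it would correspond to f = 0.45–0.62. N = 90 would then have ample power, and only the label d would be wrong. Nothing in the text supports this. The range is called Cohen's d and has to be read as such. It remains true that the wrong equivalents are certain, while the failed conclusion depends on taking that label at its word.

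Three further points deserve an answer.

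- *The upper end holds.* At d = 0.8, 30 per group gives 78–89% omnibus and 86% pairwise power. The criticism concerns the lower part of the range only.
- *Above 30 is open-ended, and 60 per group comes close for d = 0.5.* Both are true. But the section offers 30 as the threshold for the whole range and reserves larger samples for subtler effects.
- *Pairwise t tests are not the planned analysis.* This is fair as a matter of labelling, so the two definitions of d must be kept apart. The omnibus figures lead to the same conclusion on their own.

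How far selection on significance inflated the range cannot be judged without the source. That selection took place is what the section's wording indicates.

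**Conclusion.** The concern holds. The f values and sample sizes are sound. Both d equivalents are too small by a factor of about two, and the statement that more than 30 per group suffices for d = 0.5–0.8 does not survive the correction. At 30 per group, an effect of 0.5 has 38–49% omnibus or 48% pairwise power instead of 80%. At 60 per group it is borderline, at 68–81% and 78%.

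This rests on equal groups, alpha 0.05, two-sided pairwise tests, the quoted d range read as Cohen's d, and 30 or 60 per group actually analysed. If 60 were recruited and the 20% attrition mentioned under Cohorts applied, 48 per group would give 57–71% omnibus and 68% pairwise power at d = 0.5. Because the range was drawn from significant differences, true effects may well be smaller, which would lower power further.

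**What to change.** In the Power calculation section:

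1. Replace the d equivalent of f = 0.33 with about 0.70–0.81, and that of f = 0.23 with about 0.49–0.56. Say that d is the largest-minus-smallest mean difference across three equal groups.
2. Replace the conclusion about 30 per group with text such as: *30 per group gives 80% power for a two-sided pairwise comparison only when d is 0.74 or more, and 60 per group when d is 0.52 or more. For d = 0.5, pairwise power is 48% at 30 and 78% at 60 per group; for the three-group test it is 38–49% and 68–81%.* Label the pairwise figures as such, so that they are not read as the three-group d of item 1.
3. Add that the range 0.5–0.8 was taken from significant differences and probably leans high.

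The cost is a change of text. The stated detectable effects become less favourable, but design, analysis and recruitment are untouched.

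### The planning effects (d 0.5–0.8) were selected on significance and are probably optimistic, and more than 30 per group is not shown to be sufficient for them

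*Protocol article*

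**What the plan says.** The Power calculation section of the protocol article sets the target as "80% power to detect differences in proportions of immune cell populations between groups at an alpha of 0.05". It assumes an analysis of covariance with three groups, adjusted for age and sex, and gives two sizes:

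- "a sample size of 90 (30 in each group) would give sufficient power to detect an effect size of 0.33" (Cohen's f), described as "equivalent to Cohen’s d ~0.35".
- "A sample size of 180 (60 in each group) would detect an effect size of 0.23" (Cohen's f), described as d of about 0.24.

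The expected effects come from the group's own earlier flow-cytometry work on myeloid cells: "we estimated the effect sizes for significant immune cell differences between DLB, AD and controls", put at d 0.5 to 0.8. The conclusion is "This suggests that sample sizes above 30 per group would be sufficient to detect these differences", and the text adds that larger samples would pick up smaller effects. It mentions no shrinkage, no confidence limits and no subsets that failed to reach significance.

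The Analysis section plans high-dimensional clustering and gating of mass-cytometry data, to "identify key combinations of immune cell clusters that are predictive of disease phenotype and rate of decline". It does not restrict this to myeloid cells.

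**The concern.** Two things weaken the sufficiency sentence.

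First, the planning range contains only differences that had passed a significance test. That filter cuts the estimates off from below, so those that survive overstate the true effects on average. They also come from one cell lineage, while this study will look at a wider set of populations.

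Second, the d range is compared with a detectable effect at 30 per group that the protocol gives as d of about 0.35. On that figure, 0.5 to 0.8 looks comfortably covered, with room for some optimism. If the detectable d is really higher, there is no such room and the selection matters more.

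At stake is what a reader may conclude from groups of 30 or slightly more. If power at plausible effects is well below 80%, a non-significant comparison says little about whether an immune difference exists.

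**Working it through.** **Inputs.** All are from the Power calculation section: alpha 0.05, 80% power, three equal groups, two covariates, N = 90 or 180, f = 0.33 or 0.23, expected d 0.5–0.8. Assumptions of this check: d is the largest pairwise difference in residual standard deviation units; true values of 0.4 and 0.3 are illustrations, since the document gives no unselected estimate.

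**1. The stated power.** Noncentral F with df1 = 2, df2 = N − 3 − 2 and λ = N·f².

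- N = 90, f = 0.33: λ = 90 × 0.1089 = 9.80, df2 = 85, power 79.2%. Exactly 80% needs f = 0.333.
- N = 180, f = 0.23: λ = 180 × 0.0529 = 9.52, df2 = 175, power 78.8%. Exactly 80% needs f = 0.233.

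Both reproduce within rounding.

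**2. From f to d.** For three equal groups with largest pairwise difference d, f lies between d/√6 (third mean midway) and d·√2/3 (one group differs, the other two equal). Turned round, the d detectable at 80% power is:

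- 30 per group: 0.333 × 3/√2 = 0.71 to 0.333 × √6 = 0.82
- 60 per group: 0.233 × 3/√2 = 0.50 to 0.233 × √6 = 0.57

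A two-sided, two-group t test gives 0.74 and 0.52. The stated equivalents of about 0.35 and 0.24 do not follow from either route.

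**3. Power at the protocol's own range and below it.** Each cell runs from third mean midway to one group differing. Example: d = 0.5 at N = 90 gives λ = 90 × 0.25/6 = 3.75 to 90 × 0.25 × 2/9 = 5.00, hence 38–49%.

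| True d | 30 per group | 60 per group |
|---|---|---|
| 0.8 | 78–89% | 98% to over 99% |
| 0.65 | 59–73% | 90–96% |
| 0.5 | 38–49% | 68–81% |
| 0.4 | 26–33% | 48–61% |
| 0.3 | 16–20% | 29–37% |

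For 80% power, d = 0.5 needs about 59–79 per group, d = 0.4 about 92–122 and d = 0.3 about 162–216. A two-sided t test at d = 0.5 has 48% power at 30 per group and needs 63.

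**4. What selection on significance could do.** With m per group in the earlier cohort, the smallest d that reaches two-sided p < 0.05 is t(0.975, 2m − 2)·√(2/m). At m = 32 this is 2.00 × √(2/32) = 0.50. So if the groups were about equal and the test was a two-group t test, a significant d of 0.5 implies about 32 per group or more. At 15 or 20 per group the smallest significant d would be 0.75 or 0.64, which does not fit the quoted lower limit, so those sizes are left out. Simulated mean of |d| among significant results, for assumed sizes that do fit:

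| True d | m = 40 | m = 60 |
|---|---|---|
| 0.3 | 0.59 | 0.49 |
| 0.4 | 0.62 | 0.53 |
| 0.8 | 0.84 | 0.81 |

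The overstatement runs from almost nothing (0.81 for a true 0.8) to about twofold (0.59 for a true 0.3).

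**The case against.** Three points on the other side have weight.

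- **The stated power is conditional on f.** A reader might infer that selection on significance makes the 80% figures wrong. It does not: they do not depend on the earlier cohort, and they reproduce.
- **The size of the inflation is unknown.** A reader might take it as shown that 0.5–0.8 is inflated, or inflated by a given factor. The document gives neither the earlier cohort's size nor the number of subsets tested, and a large cohort with large true effects would show almost no bias. Only the expected direction is known.
- **The sentence is limited.** It speaks of the earlier differences only, says above 30 rather than 30, and is followed by a remark that larger samples detect subtler effects; a 60-per-group option is also given. A reader might infer that the protocol promises adequate power for every mass-cytometry cluster, or that null results will be read as absence of difference. It says neither.

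All three stand as limits on the point, but they do not rescue the sufficiency sentence. Read narrowly, it still says that more than 30 per group is enough for d 0.5–0.8, and at the lower end it is not, with no selection argument needed. The incorrect f-to-d equivalents are the more decisive fault. Correcting them alone would still leave a planning range chosen on its results.

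**Conclusion.** The point holds in a limited form. The planning range was taken only from significant myeloid differences and is probably optimistic, by an amount the document does not allow one to determine. The inference that more than 30 per group is sufficient for d 0.5–0.8 does not hold: 30 per group reaches about 80% power only near the top of that range and has less than 50% at the bottom. Any shrinkage lowers this further, and 60 per group then no longer guarantees 80% either.

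The power figures rest on the analysis of covariance described in the protocol, equal groups, and d taken as the largest pairwise difference; the ranges cover every position of the third mean. The figures at d = 0.4 and 0.3 are scenarios, not estimates of the true effects.

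**What to change.** In the Power calculation section:

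1. Replace the sufficiency sentence with the d detectable at 80% power: about 0.71–0.82 at 30 per group and 0.50–0.57 at 60, recomputed at the group size actually achieved.
2. State that the 0.5–0.8 range was selected on significance, comes from myeloid subsets only and is an upper-end scenario.
3. If a sufficiency statement is kept, base it on lower confidence limits, or on shrunken estimates from all subsets measured in the earlier study, including the non-significant ones. A median of absolute standardised differences would not do, because taking absolute values turns pure noise into a positive effect.

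The cost is one reworded paragraph and, for the third item, a short re-analysis of the group's own earlier work. The stated power becomes less favourable. No extra participants are needed.

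### The 29 per group in the correlation power statement is the sample size for r of about 0.50 and does not give 80% power over the lower part of the cited range (r = 0.37–0.64)

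*Protocol article*

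**What the plan says.** The second paragraph of the Power calculation section (protocol article) deals with correlations between immune markers and cognition. It moves through four statements in order:

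- An earlier mass cytometry study found "immune cell populations in AD correlating with cognitive scores with slopes of magnitude ~0.5".
- A second source is brought in as support: "A similar magnitude of correlations (r = 0.37–0.64) has been shown with immune cell subsets detected by mass cytometry and cognitive decline in AD".
- The sample size follows at once: "To detect correlations of this magnitude would require a sample size of 29 in each group", with the operating point given as "80% power at alpha = 0.05".
- A larger scenario closes the paragraph: "A sample size of 60 in each group would detect the more modest correlations ~0.35".

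The calculations are attributed to G*Power. The text does not say whether alpha is one-sided or two-sided.

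**The concern.** The sample size sentence comes directly after the range r = 0.37–0.64, so a reader will take 29 per group to be adequate across that range. A correlation of 0.37 needs far more participants than one of 0.50, because the required number grows roughly with the inverse square of the correlation. A single figure of 29 cannot hold 80% power at both.

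The layout adds to the difficulty. The article treats 0.35 as a more modest effect that calls for 60 per group, yet 0.35 lies only 0.02 below the bottom of the range that 29 is said to serve.

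What is at stake is interpretation. The relation of immune change to clinical features and progression is the second research question, and the Analysis section names cognitive decline as an outcome of interest. If a group ends with about 29 analysable participants, the present text could be cited to treat a non-significant correlation as an adequately powered negative result, when for the weaker effects in the cited range the chance of detection was near one half.

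**Working it through.** **Inputs.** From the Power calculation section: power 80%, alpha 0.05, anchor value about 0.5, cited range r = 0.37 to 0.64, stated sizes 29 and 60 per group. Assumption: two-sided test of one correlation against zero, with one-sided alpha tried as a variant.

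**Formulas.**

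- Fisher z sample size: n = ((1.960 + 0.842) / atanh(r))² + 3.
- Fisher z power: Φ(atanh(r) × √(n − 3) − 1.960).
- Exact power under bivariate normality: the noncentral t power with n − 2 degrees of freedom and noncentrality r/√(1 − r²) × √Q, averaged over Q distributed as chi-square with n − 1 degrees of freedom.

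**Step 1: reproduce the stated figures.**

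- r = 0.50: atanh = 0.5493; (2.8016 / 0.5493)² + 3 = 29.01. The exact method gives 29. The stated 29 is reproduced.
- r = 0.35: atanh = 0.3654; (2.8016 / 0.3654)² + 3 = 61.8. The exact method gives 61, and 60 per group has 79.5% power. The stated 60 for about 0.35 is correct to rounding.

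**Step 2: size needed at the lower end of the cited range.**

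- r = 0.37: atanh = 0.3884; (2.8016 / 0.3884)² + 3 = 55.0. Exact power is 79.97% at n = 54 and 80.7% at n = 55, so about 54–55 analysable participants per group.

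**Step 3: power over the range (two-sided alpha 0.05).**

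| r | Fisher z, n = 29 | Exact, n = 29 | Exact, n = 60 |
|---|---|---|---|
| 0.37 | 51% | 52% | 84% |
| 0.45 | 70% | 71% | 96% |
| 0.50 | 80% | 81% | 99% |
| 0.55 | 88% | 89% | >99% |
| 0.64 | 97% | 97.5% | >99% |

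For example, Fisher z at n = 29 and r = 0.37: 0.3884 × √26 − 1.960 = 0.021, and Φ(0.021) = 51%.

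**Step 4: how much of the range is affected.** The smallest r with 80% power at n = 29 is 0.493 (exact) or 0.500 (Fisher z). The uncovered part runs from 0.37 to about 0.49: (0.493 − 0.37) / (0.64 − 0.37) = 0.123 / 0.27, or about 45% of the range.

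**Step 5: sensitivity to method.** A one-sided alpha of 0.05 gives 65% exact power at r = 0.37 with n = 29, a smallest detectable r of 0.44, and a required n of 43–44. Treating the predictor as fixed gives 54% power at n = 29 and a required n of 52. Neither choice brings 29 per group to 80% at r = 0.37.

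**The case against.** The best defence is that the arithmetic is right and the anchor is stated. The paragraph opens with an effect of about 0.5, the cited range has its midpoint at (0.37 + 0.64) / 2 = 0.505, and the sample size phrase can be read as referring to about 0.5. The article never says outright that 29 gives 80% power at r = 0.37. The next sentence also supplies a larger size that covers the bottom of the range. Finally, the section's leading power aim concerns between-group differences in cell proportions; the correlation paragraph is secondary.

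Most of this stands. It shows that the calculation for 0.5 is correct and that the study has a scenario adequate for the whole range. It does not cure the wording: the nearest antecedent of the sample size sentence is the range itself, and over nearly half of that range the stated power is not reached.

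Three stronger readings are tempting, and the document does not support them:

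- *That 29 per group works only at r = 0.5.* It gives 80% or more at every value from about 0.50 to 0.64.
- *That 20% attrition undermines 29 or 60 per group.* The Cohorts section says: "The recruitment target detailed for each cohort allows for a 20% attrition rate over the course of the study". The numeric target is not in the text available, and the power section does not say whether its sizes are enrolled or analysed. Sizes in a power calculation are ordinarily analysable numbers, and the full protocol may give the target. A shortfall cannot be shown.
- *That a slope was wrongly used as a correlation.* The article reports populations "correlating with cognitive scores with slopes of magnitude ~0.5". Whether those slopes were standardised depends on a source that is not at hand, so no error can be established.

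**Conclusion.** The statement is wrong as worded but limited in reach. With 29 analysable participants per group and two-sided alpha 0.05, power is at least 80% for r of about 0.50 to 0.64, about 71% at 0.45 and about 52% at 0.37. The lower end of the cited range needs about 54–55 per group, nearly double the stated figure. With 60 analysable per group the whole cited range is covered.

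This rests on a single test of a correlation against zero and approximate bivariate normality. Choosing a one-sided test softens the shortfall but does not remove it. The point concerns one sentence; it does not show the study to be too small.

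**What to change.** Replace the sentence on 29 per group with wording to this effect: *29 analysable participants per group give 80% power (alpha 0.05) for correlations of about 0.50 or more; the lower end of the cited range (r = 0.37) needs about 55 per group, which the 60-per-group scenario covers (84% power).* State in the same place that alpha is two-sided, if that is what was used.

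The cost is a text edit. The claim attached to 29 per group becomes less favourable; no additional recruitment and no change to the analysis is implied.
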